### Objective 3: Cost-Effectiveness

We aim to determine whether the VPT represents value for money. The primary outcome will be quality-adjusted life years, which will be estimated based on effectiveness estimates comparing ED attendance, reattendance, and any injuries received for those engaging in the VPT service relative to those who do not. Costs will be captured from an NHS perspective, reflecting the cost of the intervention but also other costs to the NHS due to referral. A secondary cost-effectiveness analysis will undertake a societal perspective, which will explore additional costs across social care, the police, and the third sector.

### Secondary Analyses

We aim to co-produce study protocols with collaborators and Patient and Public Involvement and Engagement (PPIE) groups to provide opportunities for them to shape secondary and additional epidemiological analyses. This facilitates opportunities to realize and contribute to what is a rapidly changing policy area. One example is our inclusion of school attainment, exclusions, and attendance in analyses, which have been highlighted in these early discussions. VPUs and VRUs have made little headway working with the education system to challenge the causes of violence, and this has been identified as a priority [42]. Furthermore, additional exploration is planned to characterize those excluded from the intervention but who have available Anonymous Linkage Fields (ALFs).

### Population and Data

This is a whole-population evaluation, including all residents of Wales, United Kingdom. Data are housed in the Secure Anonymized Information Linkage (SAIL) databank [43].

### Data

#### Violence Prevention Team Data (Cardiff and Swansea)

Intervention sites record patient details (name, date of birth, and gender), NHS number, extent of engagement with the VPT, and whether any subsequent referral was made.

#### Administrative Data

Several administrative datasets are available to characterize patients and summarized in Textbox 1.

Table 1 summarizes key patient socioeconomic and demographic characteristics required to enable secondary analyses in relevant subgroups.

Emergency Department Violence Intervention Program Evaluation (EDVIPE) administrate datasets.
**The following routinely collected administrative and population datasets will be linked and analyzed to support the evaluation of the Emergency Department Violence Intervention Program Evaluation (EDVIPE).**

**Annual District Death Extract (ADDE):**

Provides week of birth and date of death, used to describe left- and right-side censoring of study participants.
**Outpatient Referral Dataset (OPRD):**

Includes data on outpatient referrals from primary care, helping to characterize referral pathways to secondary care. This dataset captures clinical referrals from General Practitioners, general and community dental practitioners, Accident and Emergency Departments, walk-in services, and consultant-to-consultant referrals.
**Patient Episode Data for Wales (PEDW):**

Covers individuals domiciled in Wales and treated in Welsh and English National Health Service (NHS) Trusts. Includes inpatient and day-case activity data, with spells and episode-level information on hospital admissions, enabling tracking of service use related to an ARA.
**Welsh Demographic Service Dataset (WDSD):**

Includes all individuals registered with a Welsh General Practitioner and, through anonymization, enables identification of household groups.
**Welsh Index of Multiple Deprivation (WIMD):**

The Welsh Government’s official measure of relative deprivation for small areas in Wales, based on 8 domains, including income, employment, health, and access to services. WIMD is typically grouped into quintiles and is included in several NHS datasets.
**2011 and 2021 UK Census:**

National censuses are conducted every 10 years that include key demographic information. Due to patient entry into and exit from the EDVIPE, some individuals may be missing from the 2011 Census (eg, born after 2011) or the 2021 Census (eg, died before 2021); therefore, data from both censuses are required.

**Table 1 table1:** Emergency Department Violence Intervention Program Evaluation (EDVIPE) patient characteristics.

Characteristic	Source
Age (from Week of Birth [WoB])	Welsh Demographic Service (WDS)
Sex	WDS, 2011 and 2021 Census
Ethnicity Asian (Bangladeshi, Chinese, Indian, Pakistani, Other Asian) Black (Caribbean, African, Other Black) Mixed (White and Asian, White and Black African, White and Black Caribbean, Other Mixed, or Multiple ethnic groups) White (English, Welsh, Scottish, Northern Irish, British, Irish, Gypsy or Irish Traveller, Roma, or Other White) Other (Arab, Any other ethnic group)	2011 and 2021 Census
Quintile of residential deprivation	Welsh Index of Multiple Deprivation (WIMD)
Urban or rural residential classification	2011 and 2021 Census

### Secondary Outcomes

To characterize the WSMA involvement of patients involved in the intervention, broader pathways will be explored across several related datasets, summarized in Textbox 2.

Emergency Department Violence Intervention Program Evaluation (EDVIPE) secondary outcomes.**Children and Family Court Advisory and Support Service (CAFCASS) Wales** family justice dataset includes information for residents of England and Wales on cases of divorce, private law, Family Law Act cases, public law, adoption, and other family law applications. It also includes information on marriage and divorce characteristics, the number of children involved in cases, and types of hearings.**Ministry of Justice (MoJ):** Data First includes linked administrative datasets covering:Magistrates’ court defendant dataCrown Court defendant dataCriminal courts and prisons dataPrisoner custodial journey dataFamily Court data**National Pupil Database (NPD)** contains 4 broad categories of data: demographics, educational attainment, absence and exclusion, and information on children in need and looked-after children.**Police Data (Police Crime Dataset):** Pending applications for police crime data from all 4 Welsh police forces are progressing and will be explored. Data sharing agreements are currently being developed to bring all-Wales police crime data into Secure Anonymized Information Linkage.**Substance Misuse Dataset (SMSD)**, also known as the Welsh National Database for Substance Misuse (WNDSM), includes data on individuals in Wales presenting for substance misuse treatment, including assessments, referrals, and treatment history.**Welsh Longitudinal General Practitioner Dataset (WLGPD)** contains clinical information from general practices in Wales, including diagnoses and referrals to secondary and tertiary care.

### Cohort Inclusion and Exclusion Criteria

All residents of Wales who are 11 years of age or older are eligible for inclusion. Residents of Wales will be defined through their identification in the Welsh Demographic Service Dataset (WDSD).

The NHS assigns each patient domiciled in the United Kingdom a unique number. This NHS number links across various NHS data systems. The encrypted and anonymized ALFs are derived from these NHS numbers. Therefore, patients attending ED whose identity cannot be connected to an NHS number (eg, overseas visitors and tourists) will not have a corresponding ALF and will, by necessity, be excluded from analyses.

### Allocation

Intervention patients will be identified in the VPT data and will have attended intervention EDs (in Cardiff and Swansea), subject to the above inclusion criteria. Control patients will be identified in the EDDS, and ED attendance was not in an intervention ED.

### Progression Criteria

This is a definitive study. As the primary focus of the study uses routinely collected data, which is available for analysis subject to information governance permissions and extraction, progression criteria are not applicable.

### Sampling

From the intervention sites’ data (Section 8.2.1), between October 2019 and December 2022, the Cardiff VPT contacted 2312 patients, of whom 77% accepted VPT support (Figure 1). We conservatively estimated that there will be 2500 patients that engaged with the Cardiff VPT across the 4 years (2019-2024) of VPT operation and a further 900 from the 2 years (2021-2024) operation in Swansea. Across the entirety of Wales, there are approximately 1 million ED attendances each year.

**Figure 1 figure1:**
[figure not shown]
Count of patients, by month, identified by the Cardiff violence prevention team (VPT) as attending due to a violence-related injury, with the number that subsequently engaged with the VPT.

Initial estimates from Cardiff VPT suggest that 3% of those engaging with the VPT reattended ED at least once within one year, compared to 23% of patients who did not engage with the VPT. Data from 2015 and 2016 suggest that the frequency of unscheduled attendances for patients with at least one ARA (mean 2.35 attendances) is greater than for patients making an unscheduled attendance without evidence of an assault (mean attendances 1.73). For a simple Cox survival model, (α=.05; β=.90), and a hazard ratio of 0.8, a total N of 845 is required.

To realize the recurrent nature of analyses, simulation [44] (1000 estimates per point estimate) was used across varying follow-up periods, which suggests a 12-month follow-up period and total N of 300 is adequate to identify a significant effect. By increasing the number of controls, statistical power will be further enhanced [45].

### Analytic Strategy

#### Objective 1: Effectiveness

##### Effectiveness Overview

Our primary outcome is unplanned ED attendance. It represents the cost to the NHS of serious health care events and acts as a proxy for events eliciting acute health care needs. EDs provide acute care for patients without prior appointment and the aftercare of patients who have received ED treatment, but where there is no alternative provision (eg, for out-of-area tourists). There can, therefore, be follow-up and planned appointments in ED. These appointments in ED will be made where, for example, there is an element of diagnostic uncertainty and a review is required in the ED context, or for patients where other follow-up arrangements are likely to fail (eg, visitors to the area without access to primary care) [46]. Follow-up and planned appointments in ED are typically a continuation of the initial unplanned attendance or referral from another health care provider and are not valid outcomes for EDVIPE, as they are not elicited in response to acute health care needs. Thus, for Objective 1 we will censor the timeline. Left-side censoring at birth or when someone takes up residence in Wales. Right-side censoring when someone dies or moves out of Wales. We further interval censor the timeline to account for repeat ED attendances associated with a health event, such as a referral from a local emergency hospital to a Major Trauma Centre (MTC).

##### Discontinuous Risk Interval

Accounting for periods when individuals are not at risk is an essential consideration in repeated time-to-event models [47-50]. The clearest example in the current context is ensuring time at risk does not extend beyond the date of death or originate before birth. Similarly, time at risk will also be left-side censored if patients move into Wales and right-side censored if they move away from Wales. With no adjustment for these discontinuous risk intervals, the time at risk will be incorrect, increasing a greater likelihood of Type II errors.

How patients are routed through emergency care pathways in Wales also influences time at risk. ED attendances are mainly determined by the acuity of the patient’s condition and the urgency with which they need to be seen. These decisions can be made by the Welsh Ambulance Service Trust (WAST), a MIU, or in the local ED. It is feasible that a patient initially attends a local ED to be stabilized, is assessed, and requires referral to a MTC or trauma unit (TU). Each MTC and TU is attached to an ED, and therefore, in response to severe injury, patients are registered in more than one ED if they are referred from an ED without trauma facilities to EDs that are attached to a TU or MTC.

In Wales, emergency care is provided in MIUs, EDs (Local Emergency Hospitals, and Rural Trauma Facilities), TUs, and MTCs. There is one MTC in Cardiff University Hospital Wales, which services South and West Wales and South Powys and acts as a TU for the local population. Morriston Hospital in Swansea is a TU, but with additional specialist services (eg, orthoplastics), meaning some patients otherwise destined for the MTC would be referred there instead. North Wales is serviced by the MTC in the Royal Stoke University Hospital in England.

Patient admission is described using spells and superspells. A spell represents patient care under a single specialty, and a superspell comprises multiple spells, where 2 spells are considered part of the same superspell if admission to the second specialty occurs within 48 hours of discharge from the first. ED attendances included within the same superspell (eg, transfer from an ED to an MTC) will therefore be attributable to the same initiating event, whether planned or unplanned. Therefore, only unscheduled attendances at the initiation of a superspell will be included, and additional ED attendances within the same superspell will be analytically censored. The duration of a superspell constitutes a discontinuity in a patient’s exposure to risk, which is then accommodated in our analytic approach; this is described further in Figure 2.

**Figure 2 figure2:**
[figure not shown]
A simplified example of discontinuous risk intervals as they relate to unscheduled Emergency Department (ED) attendance and superspells.

In Figure 2, a hypothetical analytic period runs from day 0 to day 20. Patient 1 lived in Wales for the duration of the study but had no ED attendances. Patient 2 lived in Wales at the start of the analytic period but died on day 18. They had 2 ED attendances, with the first resulting in a 2-day stay in the hospital. Their time at risk for the first ED attendance is 3 days, and for the second 6 days, with a total time at risk of 16 days. Patient 3 was born in Wales on day 2, had 3 ED attendances, and was alive and living in Wales at the end of the analytic period. However, their second ED attendance (eg, transfer to an MTC) occurred in a superspell associated with the first ED attendance, and this is dropped from consideration. They therefore had 2 ED attendances, with the time at risk for the first as 4 days and the time at risk for the second as 2 days. Their total time at risk is 10 days.

We assume that unscheduled ED attendances are independent and unordered, and therefore assume a common baseline hazard for all events. Thus, the hazard function, , for the *k^th^* ED event for each subject (*i*) is:

However, it is feasible that operational differences across Local Health Boards might influence the likelihood that ED attendance varies across groups of patients. For example, initiatives that influence the likelihood patients are conveyed into emergency care or alternative provision in the community for lower acuity patients. We introduce a random effect, , to describe variation in risk, or frailty, that can be introduced [51]:

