**Methods:**

ED patients are eligible for inclusion in the evaluation if they are normally resident in Wales, United Kingdom, aged 11 years and older. A controlled longitudinal natural experiment will be undertaken. The primary outcome is derived from the Emergency Department Dataset, routinely collected for all EDs in Wales, and is subsequent unplanned ED attendance. Case patients will be matched to control patients attending EDs without an HVIP. Analysis will derive the hazard rate for subsequent unplanned ED attendances using recurrent event analysis. The total monthly count of patients identified as attending because of violence in intervention EDs will be compared to the total count of Welsh control EDs in an interrupted time-series analysis to determine whether HVIPS increase violence ascertainment. To determine whether referral, versus no referral, to the HVIP represents value for money, we will undertake a cost-effectiveness analysis from the perspective of the National Health Service. The approval to access and analyze data housed in the Secure Anonymized Information Linkage (SAIL) databank, an ISO (International Organization for Standardization) 27001 certiﬁed and UK Statistics Authority accredited secure data environment, was granted by the SAIL independent Information Governance Review Panel (Ref: 1421). Findings will be presented at local, national, and international conferences and disseminated by peer-reviewed publication.

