### Objective 2: Ascertainment

Our second hypothesis is that intervention implementation improves ARA ascertainment.

Patients attending ED can do so repeatedly within periods of time. This frequency is likely associated with the modifiable risks associated with ARA and is of interest here. For Objective 2 it is therefore appropriate to determine the proportion of attendances identified as violence related. This generates time-series data. The outcome of interest is therefore the count of ARAs across all EDs. ARA attendance is defined as ARA in the ED PMS or, in the case of intervention sites, in the ED, PMS, or VPT data. Codes indicating the Provider Site (the ED in its hospital) are available in the EDDS, and this allows comparison between intervention EDs and control EDs. While intervention EDs have been in continual service since before the time-series start dates, this is not so for all Type I EDs in Wales; there have been several changes, with some EDs closing and others opening or being modified to receive additional patients. This, coupled with the intervention sites located at two of the largest hospitals in Wales, reduces the scope for selecting matching control sites [40], leading to potentially important baseline differences in the interrupted time-series data [41]. The counterfactual will therefore be ARAs across all control Type I EDs.

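### The primary recurrent-event model assumes that a patient's attendances are independent and gives only health-board differences as the reason for a random effect; without patient-level frailty or patient-clustered variance, its standard error is too small

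*Protocol article*

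**What the plan says.** The abstract sets the primary analysis: "Analysis will derive the hazard rate for subsequent unplanned ED attendances using recurrent event analysis". The model is given under Discontinuous Risk Interval in the Objective 1 analytic strategy: "We assume that unscheduled ED attendances are independent and unordered, and therefore assume a common baseline hazard for all events". The article then says that "it is feasible that operational differences across Local Health Boards might influence the likelihood that ED attendance varies across groups of patients", and adds one random effect "to describe variation in risk, or frailty, that can be introduced". No other reason for that term is given. Both hazard equations and the random-effect symbol are missing from the extracted text. The sections shown name no variance estimator.

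Other sections describe the source of repeat attendance differently:
- Theoretical Framework says that the risk of returning remains while a patient's underlying risks and vulnerabilities are left unaddressed.
- Objective 1: Effectiveness (design section) expects the intervention to reduce recurrence by changing those risks.
- Objective 2: Ascertainment (design section) begins "Patients attending ED can do so repeatedly within periods of time" and goes on to link that frequency to the modifiable risks behind assault-related attendance.
- Strengths and Limitations concedes that administrative data do not record the context of a patient's exposure to violence, and that risks may differ markedly between patients.

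**The concern.** One baseline hazard shared by all of a patient's events is the Andersen-Gill form. Its model-based variance treats each event as separate information, which is right only if a patient's events are independent given the covariates. If some patients carry a lasting higher risk that the covariates miss, their events cluster and the effective amount of information is smaller than the event count. A health-board effect absorbs differences between boards. It does not absorb differences between patients within a board.

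At stake are the confidence interval and P value of the primary hazard ratio. A few frequent attenders falling unevenly between the groups could look like a treatment effect. Objective 3 also draws on the effectiveness estimates.

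**Working it through.** **1. The plan's own figure.** Sampling states "α=.05; β=.90), and a hazard ratio of 0.8, a total N of 845 is required". Schoenfeld's formula, two-sided 5%, power 0.90, 1:1: 4 × (1.960 + 1.282)² / (ln 0.8)² = 42.03 / 0.0498 = 844.1, rounded up to 845. It reproduces, as a number of events. The later statement that simulation "suggests a 12-month follow-up period and total N of 300 is adequate to identify a significant effect" cannot be reproduced, because the effect size and heterogeneity used are not given.

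**2. Inputs for the check.**
- Mean events per patient, m. Sampling reports that the attendance frequency for "patients with at least one ARA (mean 2.35 attendances) is greater than for patients making an unscheduled attendance without evidence of an assault". It does not say whether 2.35 covers one year or two, or counts the index visit. Readings: 2.35 as it stands; 2.35 − 1 = 1.35; 1.35 / 2 = 0.675. Lower values are 0.5 (assumed) and 0.26, which is −ln(0.77), the Poisson rate matching the 23% of non-engaging patients who reattended within a year.
- Variance of the gamma patient frailty, k. The article gives none. Assumed range: 0.5 to 2.

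**3. Formula.** With complete follow-up, the true variance of the log rate ratio under the null is (1 + km) times the model-based one. The standard error is too small by a factor √(1 + km), and the actual type I error is 2 × [1 − Φ(1.96 / √(1 + km))].

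Worked case, m = 1.35 and k = 1: √2.35 = 1.53; 1.96 / 1.53 = 1.28; type I error 20%.

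| m | k = 0.5 | k = 1 | k = 2 |
|---|---|---|---|
| 0.26 | 6.5% | 8.1% | 11.2% |
| 0.5 | 8.0% | 11.0% | 16.6% |
| 0.675 | 9.0% | 13.0% | 20.1% |
| 1.35 | 13.0% | 20.1% | 30.8% |
| 2.35 | 18.4% | 28.4% | 41.2% |

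**4. Simulation under the null.** With N = 300, model-based tests rejected in 8.7%, 13.4% and 20.6% of runs (m = 0.675; k = 0.5, 1, 2), 13.2%, 19.3% and 30.1% (m = 1.35), and 18.8%, 27.7% and 40.6% (m = 2.35). With k = 0 they held about 5%. More patients did not help: at 6,800 and m = 2.35 the rates were 19.6%, 28.4% and 41.5%. Patient-clustered standard errors rejected in 4.4% to 6.1% of runs throughout.

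**5. Does a board term help?** Adjusting for seven boards (assumed number, between-board variance 0.05) still gave 14.3% (m = 1.35, k = 0.5), 21.1% (m = 1.35, k = 1) and 28.8% (m = 2.35, k = 1). Adding patient clustering brought these to 5.7% to 6.1%.

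**6. Power with valid standard errors.** Sampling expects 2,500 + 900 = 3,400 engaged patients, so 1:1 matching gives 6,800. At a hazard ratio of 0.8, simulated power was 1.00 for m = 1.35 and 2.35 with k up to 2. At N = 300 and m = 2.35 it fell from 0.81 (k = 0) to 0.50, 0.37 and 0.23 (k = 0.5, 1, 2).

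**The case against.** Three parts of the defence stand. First, the equations are lost, and the model is indexed by subject, so the random effect may carry a patient subscript. Second, no section says that model-based standard errors will be used; an article may leave the variance estimator to the full protocol or analysis plan. A reader might infer that the primary interval is certainly anti-conservative, but the document does not establish that. Third, the quoted sentence mainly justifies one baseline hazard instead of order-specific ones, and that choice is sound: with clustered variance the common-baseline model held about 5%.

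Other stronger readings also lack support:
- A reader might combine the 23% with m = 1.35 and solve (1 + 1.35k)^(−1/k) = 0.77, which gives k of about 10 and a standard error too small by a factor of about 3.9. But the 23% describes Cardiff patients who did not engage, and the 2.35 comes from 2015 and 2016 data with an unstated definition. The result is not an estimate for this study.
- A reader might infer that the board effect is confounded with treatment. The article does not say whether board means residence or attendance, nor which boards hold the control departments.

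The simulations omit the matching covariates, which could absorb some heterogeneity. What the defence does not remove is the stated assumption itself: independence is fixed in the text, and the only reason offered for frailty does not concern patients.

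**Conclusion.** The point holds in conditional form. The article states independence within a patient for its primary model, against its own account of why patients return, and the health-board rationale does not repair this. If the fitted model has neither patient-level frailty nor patient-clustered variance, type I error would be about 9% to 41% for means of 0.675 to 2.35, and about 6.5% to 17% for means of 0.26 to 0.5. These sizes rest on an assumed gamma frailty with variance 0.5 to 2, on unstated readings of the 2.35, on complete follow-up and on no covariates. If the missing equation does hold a patient-level term, the prose still gives the wrong reason for it and needs correcting.

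**What to change.** Replace the independence assumption with one that allows correlation within a patient. Keep the common-baseline rate model. Use patient-clustered robust (sandwich) variance for the primary hazard ratio, and report a patient-level frailty model as a sensitivity analysis. Treat any health-board effect as an additional term only, and state the level of each random effect in words.

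The cost is one modelling option and wider confidence intervals. Results reports that the Objective 1 analyses were completed in August 2025, so a rerun is needed if they were not already clustered by patient. If they were, a sentence saying so is enough.
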